## 2. Materials and Methods

### 2.1. Study Design

A simple-blind (rater) randomized controlled pilot study will be carried out using two groups: AOT (control group) and MTAO (experimental group).

### 2.2. Sample Size

The sample size calculation has been based on the projected effect of the treatment on the main outcome measure, the AHA. To detect an effect size of 1.40 [2], with a significant level of 0.05% and 80% power, a minimum of 10 participants per group will be recruited. To compensate for possible non-responses, 20% more participants will be recruited.

### 2.3. Participants

The participants will be recruited in Spain. The recruitment will be from October 2019 to March 2021. To obtain the sample, a dissemination campaign has been carried out through social networks, the Spanish infantile hemiplegia association Hemiweb and different health professionals involved in the management of these patients, following these inclusion and exclusion criteria.

Inclusion criteria:Congenital infantile hemiplegia.Aged between 6 and 12 years.Lack of use of the affected upper limb.Level I–III of the Manual Ability Classification System (MACS). Level I: handles objects easily and successfully; level II: handles most objects but with reduced quality and/or speed of achievement and level III: handles objects with difficulty; needs help to prepare and/or modify activities [32].Level I–III in the Gross Motor Function Classification System (GMFCS). Level I: can walk indoors and outdoors and climb stairs without using hands for support, can perform usual activities such as running and jumping and has decreased speed, balance and coordination; level II: can climb stairs with a railing, has difficulty with uneven surfaces, inclined or in crowds of people and has only minimal ability to run or jump and level III: walks with assistive mobility devices indoors and outdoors on level surfaces, may be able to climb stairs using a railing and may propel a manual wheelchair and need assistance for long distances or uneven surfaces [33].

Exclusion criteria:Disease not associated with congenital hemiplegia.Low cognitive level compatible with attending a special education school.Presence of contractures in the affected upper limb affecting the functional movement.Surgery in the six months previously to the treatment.Botulinum toxin in the two months previously to or during the intervention.Pharmacologically uncontrolled epilepsy.

### 2.4. Procedures and Interventions

Patients who meet the inclusion criteria will be referred by email from the recruitment centres to the researcher responsible for the project. An information meeting about the intervention protocols of both therapies will be held at the research centre with the involved families. They will then have to sign an informed consent form. Families who will accept to be included into the research will be trained in the execution of each therapy (AOT or MTAO) by an independent therapist for each therapy, teaching them how they should carry out the activities at home. In addition, they will receive a video with the activities included in the protocol. The treatment will be only initiate when the families and children will be confident about it. A weekly follow-up will be used to avoid any complications and increase the treatment adherence. The families will be requested to fill in a table with the execution time of each proposal activity in the demonstrative videos and how it is performed by the child and the behavior towards it. The follow-up with the families will be conducted online, reviewing all the problems in the activities, modifying them if it is necessary to improve the performance. The family is a key element in improving critical components (intensity, repetition, feedback) of the therapies established with the child [34]. Hadders-Algra et al. [34] state that a family-centred approach creates a richer and more varied range of opportunities by training the family to encourage the children to use the affected upper limb in their usual environment.

Two protocols are designed to be carried out at home, each lasting 20 h, applied during a four-week period (1 h per day from Monday to Friday) at home. The protocols are created based on the previous studies [25,35,36,37]. For the AOT group uni/bimanual activities are designed including 15 sets of daily life upper limb exercises: eight sets for bimanual activities and seven sets for unimanual activities (Table 1).

In the execution, the child will have to watch the video and execute the observed action in the best possible way. The observed action will be repeated for 4 min. All the activities included in the protocol will be observed and imitated during a total time of 60 min without resting periods. During the sessions, each child should sit on a chair with both arms on a table in front of a monitor screen placed 1 m away. The parent will sit on the child’s affected side and should encourage the child by giving verbal suggestions without making any demonstration.

For the MTAO group, the first 15 min will be assigned to the mirror therapy and the remaining 45 min to the action observation therapy. In the first part of the mirror therapy, six activities to be performed with both upper limbs/hands symmetrically have been designed. Even if the affected upper limb cannot successfully complete the proposed action, the child will be asked to do it to the best of his or her ability. (Table 2).

The action observation therapy will be carried out for 45 min (after mirror therapy), using the same activities as in the AOT group (Table 2) and the same positioning of the child, but in this group 3 min are allocated for the visualization and execution of each set without resting during the execution.

Both protocols will include 60-min sessions. The MTAO protocol, begins with 15 min of mirror therapy, followed by 45 min of AOT with a duration of 3 min for each activity, in order to complete 60 min.

The randomization method will be carried out using the Epidat v. 4.2 software (Consellería de Sanidade, Xunta de Galicia, 15703, Spain), which, after a simple randomization process and consecutive sampling, will divide the participants into two groups (TOT and MTAO) with a number of 10 participants per group. A numerical sequence will be obtained which will be kept in opaque sealed envelopes. The envelopes will be opened by a blind researcher, who will decide at random, according to the randomization sequence. Although subject recruitment has begun, due to the Coronavirus pandemic, the trial has been delayed until the follow-up of participants can be ensured.

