### 2.6. Data Analysis

Statistical analyses will be performed with SPSS v.24.0 (SPSS Inc., IBM, Chicago, IL, USA). Statistical significance will be set at *p* < 0.05. The test Shapiro-Wilk test will be used to study normality of the sample.

A descriptive analysis of demographic variables will be performed using means and standard deviation for normal distribution variables, and medians and interquartile ranges for non normal distribution variables. The categorial variables will be described using frequencies and %.

To evaluate statistically significant differences intergroup in the variables at baseline, the independent Samples T-test (normal distribution) or the Mann-Whitney U test (non normal distribution) will be used. To study the effects of the interventions on the outcomes measures at four time points, for normal distribution variables, a two-way (intervention × time) repeated measures ANOVA test will be conducted. The Bonferroni correction will be employed for pairwise post-hoc comparisons to further analyze significant interactions. The Greenhouse–Geisser adjustment will be applied to correct for the lack of sphericity (Mauchly’s sphericity test, *p* < 0.05) whenever is necessary. For non-normal distribution variables, the Friedman test will be used. Bivariate correlation coefficients will be estimated to examine the relationship between the subjects’ age, sex, or affected upper limb.

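### Section 2.4 describes allocating 10 children per group, without the 20% allowance of section 2.2, and names simple randomisation, which does not guarantee 10 per group

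*Protocol article*

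**What the plan says.** Section 2.2 (Sample Size) bases the calculation on the Assisting Hand Assessment: "To detect an effect size of 1.40 [2], with a significant level of 0.05% and 80% power". The result is that "a minimum of 10 participants per group will be recruited". The next sentence adds an allowance: "To compensate for possible non-responses, 20% more participants will be recruited".

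Section 2.4 (Procedures and Interventions) describes the allocation. Software will run a "simple randomization process and consecutive sampling, will divide the participants into two groups (TOT and MTAO) with a number of 10 participants per group". It continues: "A numerical sequence will be obtained which will be kept in opaque sealed envelopes". The length of that sequence is not given. No block, restriction or equal-size rule is named.

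Section 2.6 (Data Analysis) gives the test level: "Statistical significance will be set at *p* < 0.05". Section 2.1 calls the study a pilot in which the rater is blinded. Section 2.5 follows the children to 6 months after treatment.

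**The concern.** Two statements do not fit together.

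- **Number.** Section 2.2 recruits for 24 children, while section 2.4 describes the division of 20. If staff follow section 2.4, the allowance for loss never reaches the randomised sample, and any loss comes out of the 10 per group that the power calculation needs.
- **Method.** Simple randomisation leaves the group sizes to chance, yet section 2.4 gives a fixed size. Either the arms will usually not be 10 and 10, or some restriction is applied that the text does not name.

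At stake is the stated 80% power on the main outcome, in a trial with home treatment and assessments up to 6 months afterwards. It must also be possible to carry out the allocation as the protocol describes it.

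**Working it through.** **Inputs**

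- Effect size d = 1.40, power 80%, minimum 10 per group, 20% more recruited: section 2.2.
- Simple randomisation, 10 per group: section 2.4.
- Significance level 0.05: section 2.6. Section 2.2 prints this level as a percentage (0.05%). Read literally (0.0005) it would need 23 per group by t-test, so the stated 10 fits only 0.05. That slip is a separate matter.
- Two-sided testing is an assumption, because sidedness is not stated.

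**Step 1. Reproduce the plan's figure.** Two-sample t-test, noncentrality d × √(n₁n₂/(n₁+n₂)), with n₁+n₂−2 degrees of freedom:

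| Per arm | Noncentrality | Power |
|---|---|---|
| 8 | 1.40 × √4 = 2.80 | 74.0% |
| 9 | 1.40 × √4.5 = 2.97 | 79.6% |
| 10 | 1.40 × √5 = 3.13 | 84.1% |

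The smallest n reaching 80% is 10, as section 2.2 states. The normal approximation gives 9 and a one-sided t-test gives 8, so neither is the basis of the stated figure.

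**Step 2. Total with the allowance.** 10 × 1.2 = 12 per arm, 24 in all. If the allowance is meant to leave 10 after a 20% loss, 10/0.8 = 12.5, rounded up to 13 per arm, 26 in all. Section 2.4 gives 2 × 10 = 20.

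**Step 3. Effect of the missing allowance.** If 20 are randomised and 20% are lost, 20 × 0.8 = 16 remain, or 8 per arm, with 74.0% power. One loss per arm (9 and 9) already gives 79.6%. If 24 are randomised in equal arms, 24 × 0.8 = 19.2 remain; a 10:9 split has 81.9% power.

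**Step 4. What simple randomisation of 20 gives.** Group size is Binomial(20, 0.5):

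- P(10:10) = C(20,10)/2²⁰ = 184,756/1,048,576 = 17.6%
- P(7:13 or worse) = 26.3%
- P(6:14 or worse) = 11.5%

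**Step 5. Power cost of imbalance alone, no loss.**

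| Split of 20 | Power |
|---|---|
| 10:10 | 84.1% |
| 8:12 | 82.6% |
| 7:13 | 80.6% |
| 6:14 | 77.4% |

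Power is below 80% only at 6:14 or worse. With 24 children, at least one arm falls below 10 in 30.7% of lists, but this is not a power failure: a 9:15 split of 24 has 88.7% power.

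**The case against.** The best defence is that section 2.4 merely repeats the minimum of 10 from section 2.2, and that its wording describes a random division into two equal groups, with the word simple used loosely to mean unstratified. On that reading the allowance is intended and only the wording is at fault. This is plausible and limits what can be claimed. Even so, section 2.4 would still misstate the number randomised and misname the method.

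Several stronger readings should be resisted.

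- A reader might infer that the randomisation list ends at 20. The length of the sequence is not printed, so this is only an inference from the group size.
- A reader might say that simple randomisation cannot give 10 per group. It can, in 17.6% of lists of 20; it does not guarantee it.
- A reader might infer that unequal arms threaten the power. Step 5 shows that they mostly do not.
- A reader might infer a long run of predictable late allocations, on the assumption that an arm is closed once it reaches 10. The document describes no such procedure. It specifies opaque sealed envelopes opened by a blinded researcher.

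It is also fair to say that the study is a declared pilot and that the 74% needs two conditions: only 20 randomised, and the full 20% lost. Both stand as qualifications. The second condition, however, is the loss that section 2.2 itself plans for.

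**Conclusion.** The concern holds in a limited form. Sections 2.2 and 2.4 disagree on the number of children (24 or 26 against 20), and section 2.4 names a method that does not secure the group sizes it states.

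The material consequence comes from the allowance: followed as written, a 20% loss leaves 8 per arm and about 74% power, 6 percentage points below the stated 80%. This assumes d = 1.40, a two-sided 0.05 t-test (the basis that reproduces the stated 10) and losses spread equally over the arms. On the normal approximation, 8 per arm would give 79.96%, but that approximation does not reproduce the stated 10.

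The choice of simple randomisation is mainly a problem of consistency and has only a small power cost. Confidence is high on the conflict in the text. Whether only 20 would in fact be randomised cannot be told from the document.

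**What to change.** 1. In section 2.4, state one total to be randomised that includes the allowance, and make it agree with section 2.2: 24 (12 per arm), or 26 (13 per arm) if the allowance is taken as n/0.8.
2. Replace simple randomisation by a named restricted method that gives equal arms. A random permutation of the full list would do, as would concealed blocks of varying size larger than 2. Blocks of 2 are best avoided, because every second allocation is determined and only the rater is described as blinded.
3. Keep the sealed envelopes. Apply the change to children not yet allocated. Section 2.4 says that recruitment has begun and the trial is delayed, but not whether any child has been allocated.

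The cost is a regenerated list and a sentence or two. A total of 24 needs no children beyond the 20% more already planned; 26 adds two. The small downside is that some late allocations become more predictable than under unrestricted randomisation.

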### 2.5. Outcome Measures

Four assessments will be performed. The first assessment will be focused on obtaining the data before the treatment and sociodemographic variables (including age and sex), i.e., in week 0 (baseline situation, immediately before starting treatment), whereas the second assessment will be conducted at the end of the treatment, i.e., in week 4 (a total dose of 20 h). Moreover, two follow-up assessments will be done: 3 month and 6 months after treatment in both protocols (Figure 1).

#### 2.5.1. Spontaneous Use

Spontaneous use will be measured using the AHA v. 5.0 scale [38], which is validated for children with infantile hemiplegia and obstetric brachial palsy from 18 months to 12 years. Considering the age range of the participants in this study, the School Kids AHA v. 5.0 Scale will be used, a valid and reliable tool that includes 20 items, with a score from 1 (non-performance) to 4 (effective use) [39,40,41]. The play session will be videotaped and subsequently scored by a trained evaluator and blinded to the group assignment. The Rasch model provides equal interval measures in logits (logarithmic probability units) by converting ordinal rating scale observations into interval levels. In order to facilitate the interpretation of the results, the logit scale is converted into a user-friendly scale from 0 to 100 that continues to be based on the Rasch model and presents interval level data (i.e., AHA) [39].

#### 2.5.2. Manual Ability

Manual ability will be assessed with the JTHFT. This standardized test of simulated functional tasks that quantifies the time to complete a battery of one-handed activities [34]. Activities performed with the paretic hand include turning cards, placing objects, simulating eating, stacking tokens, and manipulating empty and full cans. The JTHFT has shown excellent reliability (0.95–0.99) in children with hand disabilities. [42,43]. The session will be also videotaped and subsequently scored by a trained evaluator and blinded to the group assignment.

#### 2.5.3. Surface Electromyography (EMG) of Extensors and Flexors Muscles of the Wrist

Surface EMG (mDurance Solutions, Granada, Spain) will be used to analyze the muscle recruitment and coordination during maximum isometric contraction. The children will be seat comfortably in a chair. Both shoulders will be at a position of slight flexion and abduction. The elbow will be at flexion, the forearm at neutral position and the hand will be placed naturally on the table. To produce the maximum isometric contraction, children will be asked to grip a cylindrical wood piece. The surface electrodes (36 × 45 mm) will be attached to the skin of the flexor and extensor muscles of the wrist and being parallel to the muscle fibers direction. Previously, the skin will be cleaned using 70% alcohol and fine paper. Three trials of 10 s will be recorded, with a rest of 10 s between trials. Before collected the EMG signals, no contraction signals will be on the screen. The children must avoid intense exercise prior to the test to exclude the effect of residual fatigue. The affected hand will be evaluated first. The root mean square (RMS), integrated EMG (iEMG) and cocotraction ratio (=iEMG of wrist flexors/[iEMG of wrist extensor + iEMG of wrist flexors] × 100) will be calculated and analyzed [14,44,45].

#### 2.5.4. Grasp Strength

In addition, a grip dynamometer (Kern, Balingen, Germany) will be used to assess the grasp strength. The children will be seated in the same position as for the EMG evaluation. The involved hand will be assessed first and then, the non-involved hand. The children will be asked to grasp the dynamometer for 10 s. Three trials will be recorded with a resting interval of 10 s. The grasp dynamometry is a valid and reliable test in cerebral palsy children [46,47].

### 2.6. Data Analysis

Statistical analyses will be performed with SPSS v.24.0 (SPSS Inc., IBM, Chicago, IL, USA). Statistical significance will be set at *p* < 0.05. The test Shapiro-Wilk test will be used to study normality of the sample.

A descriptive analysis of demographic variables will be performed using means and standard deviation for normal distribution variables, and medians and interquartile ranges for non normal distribution variables. The categorial variables will be described using frequencies and %.

To evaluate statistically significant differences intergroup in the variables at baseline, the independent Samples T-test (normal distribution) or the Mann-Whitney U test (non normal distribution) will be used. To study the effects of the interventions on the outcomes measures at four time points, for normal distribution variables, a two-way (intervention × time) repeated measures ANOVA test will be conducted. The Bonferroni correction will be employed for pairwise post-hoc comparisons to further analyze significant interactions. The Greenhouse–Geisser adjustment will be applied to correct for the lack of sphericity (Mauchly’s sphericity test, *p* < 0.05) whenever is necessary. For non-normal distribution variables, the Friedman test will be used. Bivariate correlation coefficients will be estimated to examine the relationship between the subjects’ age, sex, or affected upper limb.

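### The planned 2 × 4 ANOVA interaction does not itself estimate the MTAO–AOT difference in AHA; one pre-specified, baseline-adjusted contrast would answer the hypothesis better and tolerate missed visits.

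*Protocol article*

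**What the plan says.** - **Main analysis (section 2.6, Data Analysis).** For normally distributed outcomes measured at four time points, "a two-way (intervention × time) repeated measures ANOVA test will be conducted". The follow-up step is: "The Bonferroni correction will be employed for pairwise post-hoc comparisons to further analyze significant interactions". The text does not say how many comparisons form the Bonferroni family, nor whether they compare arms at a visit or visits within an arm. Non-normal outcomes go to the Friedman test; this point concerns the ANOVA route.
- **Baseline (section 2.6).** Significance tests are planned: "To evaluate statistically significant differences intergroup in the variables at baseline". Baseline is also one of the four time levels in the ANOVA. It is not a covariate.
- **Sample size (section 2.2).** "The sample size calculation has been based on the projected effect of the treatment on the main outcome measure, the AHA". The inputs are given as "To detect an effect size of 1.40 [2], with a significant level of 0.05% and 80% power", and "a minimum of 10 participants per group will be recruited", with a further 20% to cover non-response. No test, time point or contrast is named.
- **Hypotheses (section 1).** They are directional and between arms: MTAO is expected to raise spontaneous use more than AOT.
- **Visits (section 2.5).** Baseline, week 4, and 3 and 6 months after treatment.

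**The concern.** The trial needs one statement: by how much MTAO differs from AOT on AHA, and when. The interaction has 2 − 1 = 1 degree of freedom for arm times 4 − 1 = 3 for time. A significant result says only that the two profiles are not parallel. The size, direction and timing must come from the pairwise step, whose family is left open, so the decisive comparison and its alpha are not fixed in the text.

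Two further features cost information in a trial of about 20 children. Baseline AHA enters as a repeated measure rather than as a covariate. And classical repeated-measures ANOVA needs all four values, so a child seen at week 4 but missed at 6 months contributes nothing, not even the week-4 score. The protocol itself allows for 20% non-response.

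**Working it through.** **Step 1. Reproduce the stated size.** Inputs from section 2.2: d = 1.40, power 80%, n = 10 per group. Section 2.2 prints alpha as 0.05%, whereas section 2.6 says "Statistical significance will be set at *p* < 0.05". Exact power of a two-sample t-test uses noncentrality d·√(n/2) with 2n − 2 df:
- n = 10, two-sided 0.05: 1.40 × √5 = 3.13 on 18 df, power 84.1%.
- n = 9: power 79.6%. So 10 is the smallest n that reaches 80%.
- One-sided 0.05 needs 8 per group. Alpha taken literally as 0.0005 needs 23.

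The stated 10 matches one two-sided two-group comparison at 0.05.

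**Step 2. One visit after Bonferroni.** Same n and d, unadjusted arm comparison at one visit, for different family sizes (the family is an assumption):

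| Tests in family | Alpha | Power |
|---|---|---|
| 1 | 0.05 | 84.1% |
| 3 | 0.0167 | 68.6% |
| 4 | 0.0125 | 64.1% |
| 6 | 0.0083 | 57.5% |

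**Step 3. Covariate against change from baseline.** With unit SD and correlation ρ between baseline and week 4, the residual variance is 2(1 − ρ) for a change score and 1 − ρ² with baseline as covariate. The ratio is 2/(1 + ρ): 1.33, 1.18 and 1.05 at ρ = 0.5, 0.7 and 0.9. The gain is real but small when ρ is high.

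**Step 4. Complete data, 10 per group, d = 1.40.** Simulation with compound symmetry and Greenhouse–Geisser interaction. ρ is assumed, not in the document. Sustained means the full effect at all three later visits; partly fading means 100%, 50% and 25% of it.

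| ρ | Interaction, sustained | Interaction, partly fading | Baseline-adjusted week 4 |
|---|---|---|---|
| 0.5 | 86–87% | 72–73% | 91% |
| 0.7 | 98% | 92–93% | 98% |
| 0.9 | 100% | 100% | 100% |

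Ranges reflect simulation error between runs. Under the null, rejection rates were near nominal: 4.0% for the interaction and 5.2% for the adjusted contrast.

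**Step 5. Missed visits.** Assume 12 per group (10 × 1.2) and independent misses at each of three post-baseline visits. A week-4 analysis of covariance on available data stands in for the mixed-model contrast.
- 10% per visit: complete cases 24 × 0.9³ = 17.5; children with a week-4 AHA 24 × 0.9 = 21.6. At ρ = 0.5, interaction power is 78–80% (sustained) or 63–64% (partly fading), against 92–93% for the adjusted contrast. At ρ = 0.7 it is 95–96% or 86–87%, against 98%.
- 20% per visit: complete cases 24 × 0.8³ = 12.3; with week 4, 24 × 0.8 = 19.2. At ρ = 0.5, interaction power is 54% or 40%, against 88%.

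**Step 6. Selective loss, as illustration.** Suppose control children whose AHA fell by week 4 miss each later visit with probability 0.5 and everyone else with 0.05. The complete-case difference in week-4 change then falls from a true 1.40 to 1.06 (ρ = 0.7) or 0.97 (ρ = 0.5). The adjusted contrast on all week-4 data stays at 1.41.

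**The case against.** Several stronger readings are tempting, and the document does not support them.

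- **Baseline imbalance is ignored.** It is not. Baseline is a time level, so a constant difference between arms cancels out of the interaction. What stands is lower efficiency (step 3), and that a between-arm pairwise test at a single visit would be unadjusted, if that is what is meant.
- **The trial really has 64% power.** That figure assumes a family of four between-arm tests, one of them at baseline. Other readings do better. After a significant interaction and with a sustained effect, a week-4 comparison at 0.05 has 75%, 83% and 84% power at ρ = 0.5, 0.7 and 0.9, and a change-from-baseline contrast at 0.05/3 has 67%, 90% and 100%. The defect is that the text does not say which applies.
- **The planned test contradicts the powered test.** Section 2.2 names no test, and the effect size comes from a cited source not available here. The mismatch is inferred from the arithmetic.
- **The ANOVA is wrong or always weaker.** With complete data it is valid, and for a sustained effect its power is close to that of the adjusted contrast.
- **The plan says incomplete children are dropped.** It does not. This is a property of the classical procedure, and missing-data handling may be set out in a document not shown. Section 2.2 does not say that its 20% means missed visits.

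It is also fair to say that the advantage depends on the contrast chosen. If the effect fades to zero by 6 months, a post-baseline average has 61% power against 83% for the interaction at ρ = 0.5. Nothing in the protocol makes week 4 primary. The pilot label in section 2.1 lowers the stakes, but the article still states superiority hypotheses and an 80% power target.

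**Conclusion.** The point holds as a weakness of choice and specification, not as an invalid analysis. The stated method does not deliver the quantity in the hypotheses, and the step that could deliver it is left open. A baseline-adjusted contrast gains little with complete data and a sustained effect (91–100% against 86–100%). It gains more if the effect partly fades (91% against about 72% at ρ = 0.5) or if visits are missed (about 92% against 80% at ρ = 0.5 with 10% missed and a sustained effect). These comparisons assume d = 1.40, compound symmetry, ρ from 0.5 to 0.9 and the stated missingness; only d comes from the document. The bias in step 6 depends wholly on its assumed dropout pattern and shows what could happen, not what will. That the interaction lacks size, direction and timing rests on none of these assumptions.

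**What to change.** 1. Name one MTAO–AOT contrast in AHA at one time point as the single confirmatory test at 0.05, reported with its 95% CI. Week 4, the end of treatment, is one example; the investigators should commit to the visit that matches their claim.
2. Estimate it with a linear mixed model (SPSS MIXED, REML): arm, post-baseline visit, arm-by-visit, and baseline AHA as covariate. Use a simple covariance structure with small-sample degrees of freedom, since about 20 children will not support a rich one. Include all randomised children with available visits, in the arm to which they were allocated.
3. Report the other visits and outcomes as secondary.
4. Drop the baseline significance tests; describe baseline by arm instead.
5. State in section 2.2 that the sample size refers to this contrast, and reconcile the printed alpha of 0.05% with the 0.05 in section 2.6.

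The cost is a change of wording in software already planned, to be made before any unblinded analysis. The downsides are one degree of freedom for baseline, a covariance structure to choose in advance, and commitment to one time point, which would miss an effect that appears only at another visit.
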